## Abstract

**Background:**

Statistics show that every year, 5.4 million people in the world suffer a stroke. Post-stroke cognitive impairment (PSCI) is one of the most common complications after stroke with a rate of 75%, which leads to decreased functions for independent living and reduced quality of life (QOL). Exercise training has been reported to be useful to improve the cognitive functions of post-stroke patients. Yijinjing, a traditional Chinese Qigong exercise characterized by an integration of mind and body in moderate exercise intensity, can improve cognitive functions of PSCI patients. This study aims to explore the feasibility and effectiveness of the Yijinjing exercise in this regard.

**Methods:**

A single-blind, superiority, randomized controlled trial will be employed with evaluations at 3 and 6 months. Seventy-two PSCI patients will be recruited and randomly assigned to the Yijinjing exercise intervention group or the control group (1:1). Participants in the control group will receive routine rehabilitation therapies, including occupational therapy, physical therapy, acupuncture therapy, and health education 5 times a week for 3 months. The intervention group will receive a 12-week routine rehabilitation therapy combined with the Yijinjing exercise intervention for 40 min each session and 3 sessions a week. The primary outcome of cognition will be measured by the Montreal Cognitive Assessment scale (MoCA). Secondary outcomes include executive function, memory function, visuospatial function, sleep quality, gait and motor function, activity of daily living (ADL), and quality of life (QOL).

**Discussion:**

Current evidence has reported the effectiveness of traditional Chinese exercise in improving the post-stroke population’s motor functions. This research is a randomized controlled trial that evaluates traditional Chinese exercise’s effectiveness for PSCI patients. It is expected to expand the traditional Chinese exercise scope and provide a new treatment approach for stroke populations with cognitive impairments.

**Trial registration:**

Chinese Clinical Trial Registry ChiCTR1900026532. Registered on 13 October 2019.

## Background

According to the World Health Organization (WHO), 6.2 million individuals die of stroke every year, while about 5.4 million survive [1]. Studies have shown that 75% of stroke patients live with cognitive impairments [2]. Post-stroke cognitive impairment (PSCI) is one of the most common factors leading to lifelong disabilities after stroke, which significantly impacts the patients’ activities of daily living (ADL) and their quality of life (QOL) [3, 4]. Moreover, healthcare and caregiving costs are high, which poses an economic burden for the healthcare system and families [5].

The symptoms of PSCI mainly include decreased memory, short attention span, decreased executive function, and dyscalculia. Side effects and clinical limitations of pharmacological therapy have been reported [6–8]. Mainstream post-stroke rehabilitation is based on neuroplasticity theory, which believes that repetitive practice after stroke can facilitate new synapses in the brain, thereby improving brain function [9]. As a non-pharmacological approach, exercise therapy has become a feasible strategy to improve PSCI [10, 11]. However, limited motor functions and decreased endurance due to stroke could prevent a post-stroke patient from participating in exercise activities. Low- or moderate-intensity mind-body exercise addresses physical and mental functions, which would be appropriate for this population, especially the older adults. Previous studies have shown that mind-body exercise can potentially improve motor function, psychological function, and ADL of stroke patients [12, 13] . As one of the traditional Chinese exercises, Yijinjing is a moderate-intensity exercise therapy based on traditional Chinese medicine theory. The Yijinjing exercises emphasize the combination of symmetrical physical postures, meditative mind, and breathing techniques in a harmonious manner. The Yijinjing exercise consists of linear movements and requires isolated joint movements. With simplified patterns and directions, Yijinjing is easy to practice with few limitations. The pilot study has demonstrated that the Yijinjing exercise helped improve older people’s physical and psychological outcomes in the community. This study’s primary purpose is to conduct a randomized controlled trial to evaluate the Yijinjing exercise’s effects in improving the cognitive functions of PSCI patients.

### Hypothesis

The Yijinjing exercise positively affects the cognitive functions, sleep quality, ADL, and QOL of PSCI patients.The Yijinjing exercise has better outcomes, compared with the routine treatment for PSCI patients.

## Methods/design

### Objectives

The objectives of this study are:
To evaluate the Yijinjing exercise’s effectiveness for treating PSCI;To test whether the Yijinjing exercise is more advantageous than routine treatment for PSCI patients;To explore the feasibility of developing the Yijinjing exercise as an approach to improve the cognitive functions of the PSCI population.

### Study design

A single-blind, superiority, randomized controlled trial (RCT) will be employed to compare the Yijinjing exercise with routine treatment. Seventy-two post-stroke patients with mild cognitive impairment from Yueyang Hospital of Integrated Traditional Chinese and Western Medicine and Shanghai Jinhui Rehabilitation Hospital will be recruited. Before receiving the rehabilitation, the demographic information, such as name, gender, age, educational background, and medical history of all participants will be collected. SPSS software will generate a table of numbers that will be used to randomly assign all eligible patients to the control group (routine treatment) or the Yijinjing group (the modified Yijinjing exercise) at a 1:1 ratio. The intervention will be implemented for 12 weeks. All assessments will be conducted before the intervention, after the intervention, and 3 months after the intervention (see Fig. 1). The schedule for the study is shown in Fig. 2.

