### Setting and recruitment

All participants will be recruited at Yueyang Hospital of Integrated Traditional Chinese and Western Medicine and Shanghai Jinhui Rehabilitation Hospital. Both hospitals will post research advertisements to recruit participants. To enhance recruitment quality, the chief investigator will monitor medical records. Recruitment will be carried out by two study researchers, who will carefully record the participants’ past and present medical history.

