### Eligibility criteria

#### Inclusion criteria

The eligible patients have to meet the following criteria: (1) the clinical diagnosis of stroke according to the Fourth National Academic Conference on Cerebrovascular Diseases Diagnostic Criteria for All Kinds of Cerebrovascular Disease [14] and confirmed by CT or MRI, (2) within 1 year of onset, (3) aged 60–75 years, (4) mild cognition impairment: MoCA< 26 (if the length of schooling is ≤ 12 years, then 1 point will be added to the examination result), (5) balance function: 21 < Berg score < 40, and (6) agreement on participation and signing the informed consent.

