### Randomization and allocation concealment

To reduce the chance of bias and increase the probability of meeting statistical analysis assumptions, the chief investigator will receive a computer-generated random list using the statistical software SPSS 24.0 from a statistician independent of the analysis and research teams. Then, the chief investigator will inform the coaches, therapists and participants about the treatment and follow-up plan. Before the first treatment and after the treatment is completed, the assessors will be notified to evaluate all participants.

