#### Routine treatment group

With 5 PTs, 5 OTs, and 5 acupuncture physicians providing treatment, the routine treatment group will receive regular rehabilitation services delivered by certified physical therapists, certified occupational therapists, and certified acupuncture physicians, which will be carried out following the inpatient treatment plan. Besides, all participating therapists will be uniformly trained before starting this research to standardize the treatment further. The rehabilitation services include physical therapy (exercise therapy, balance training, joint mobilization), occupational therapy (homework training, hand training, cognitive dysfunction training), acupuncture therapy, and health education.

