### Statistical analysis

Statistical analyses will be carried out using SPSS software version 24.0 (SPSS, Inc., Chicago, IL, USA) and Microsoft Excel 2016 software. Data will be presented as means, standard deviations, and percentage changes. The intention to treat (ITT) principle will be used for statistical analysis, and the multiple imputation will reduce the missing data. Repeated measures ANCOVA will be applied for each measure to compare test performance between the Yijinjing exercise and routine treatment, with baseline scores used as covariates. Statistical significance will be considered at *p* value < 0.05.

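### The stated ANCOVA adjusts for baseline scores only, leaving hospital and time since stroke out of the model at a modest cost in precision

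*Protocol article*

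**What the plan says.** All of the following is in the protocol article.

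- **Sites** (Setting and recruitment): "All participants will be recruited at Yueyang Hospital of Integrated Traditional Chinese and Western Medicine and Shanghai Jinhui Rehabilitation Hospital". By their names, one is an integrated-medicine hospital and the other a rehabilitation hospital. Each advertises for its own participants: "Both hospitals will post research advertisements to recruit participants".
- **Time since stroke** (Inclusion criteria): patients qualify if they are "within 1 year of onset".
- **Comparator** (Routine treatment group): routine rehabilitation, "which will be carried out following the inpatient treatment plan". The same section says that the therapists are trained to a common standard beforehand.
- **Allocation** (Study design; Randomization and allocation concealment): "SPSS software will generate a table of numbers that will be used to randomly assign all eligible patients" at 1:1, and "the chief investigator will receive a computer-generated random list using the statistical software SPSS 24.0". Neither section says whether the list has blocks or strata.
- **Model** (Statistical analysis): a repeated measures ANCOVA is fitted for each outcome to compare the two arms. The only adjustment it names is "with baseline scores used as covariates". Hospital and time since onset do not appear.

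**The concern.** The covariate set is stated outright, so the omission of hospital and time since onset can be read from the text and is not inferred from silence. Both are plausible predictors of outcome. Two hospitals of different type may differ in case mix and in the inpatient plan that routine care follows. A window running from recent onset to 1 year is likely to mix patients at different stages of recovery.

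Two things are at stake. First, variance that these factors explain beyond the baseline score stays in the residual and widens the confidence interval for the treatment effect. Second, if the arms happen to differ in hospital mix or time since onset, the stated model does not correct for it. The planned power has little margin above 0.80, and the Discussion section itself lists an insufficient sample size as a limitation. A cheap gain in precision is therefore worth having.

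**Working it through.** **Inputs from the article (Sample size estimation).** Effect size f = 0.3, α = 0.05, target power 0.80, 2 groups, m = 3 measurements, minimum N = 62, then 72 after 15% attrition.

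**Assumed, because the documents do not give them.** The correlation between measurements, ρ = 0.5. The share R² of residual variance that hospital and time since onset explain beyond the baseline score: 2%, 5% and 10%.

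**Step 1: reproduce the stated N.** For the between-groups F test in a repeated measures ANOVA, the noncentrality is λ = f²·N·m / [1 + (m − 1)ρ], with 1 and N − 2 degrees of freedom.

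- N = 62: λ = 0.09 × 62 × 3 / 2 = 8.37, power 0.812.
- N = 60: λ = 8.10, power 0.799.

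With equal arms, 62 is the smallest N that reaches 0.80, so the plan's figure reproduces under ρ = 0.5. The attrition step gives 62 × 1.15 = 71.3, rounded up to 72; 62 / 0.85 would give 73. The stated sample size does not depend on the present point.

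**Step 2: gain from adding the two covariates.** Removing a share R² of the residual variance multiplies the standard error by √(1 − R²) and turns the effect size into f / √(1 − R²), so λ becomes 8.37 / (1 − R²). This takes the plan's f = 0.3 as the effect size before the two covariates are added.

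| Assumed R² | SE multiplier | λ at N = 62 | Power at N = 62 |
|---|---|---|---|
| 0 | 1.000 | 8.37 | 0.812 |
| 2% | 0.990 | 8.54 | 0.820 |
| 5% | 0.975 | 8.81 | 0.832 |
| 10% | 0.949 | 9.30 | 0.851 |

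The gain is about 1 to 4 percentage points of power.

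**Step 3: cost if the covariates explain nothing.** The denominator degrees of freedom fall from 60 to 58 and λ stays at 8.37. Power goes from 0.8123 to 0.8119, a loss below 0.001. In the other rows of the table the 2 degrees of freedom also cost less than 0.001.

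**Step 4: how often the arms would differ by chance.** The site split is not given, so take 36 patients per hospital. If the list fixes the arms at 36 and 36 but does not control hospital, the share of patients from a given hospital differs between arms by 20 percentage points or more with probability 0.098 (hypergeometric). Simple randomisation gives about 0.08. For time since onset, the standardised difference between arms has standard error √(2/36) = 0.236. A difference of 0.3 or more therefore has probability about 0.20 (z = 1.27), and of 0.5 or more about 0.03 (z = 2.12). The hospital figures would not apply to a list stratified by hospital; stratifying by hospital would not control time since onset.

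**The case against.** **No stated figure is wrong, and the gain is unquantified.** This is largely fair. The sample size reproduces, the plan reaches its own power target without the extra covariates, and R² has no source in the documents. At 2% the benefit is under one point of power. That limits the weight of the point but does not remove it, because the cost in Step 3 is close to nil.

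**Chance imbalance under valid randomisation is not bias.** This stands. The test keeps its type I error, and adjustment for the baseline score already removes imbalance that acts through baseline level. Only the part that acts beyond baseline remains.

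**Routine care is shared by both arms and delivered by uniformly trained therapists.** This also stands, and it weakens the idea that the comparator differs by hospital. It does not remove differences in case mix between the two hospitals.

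**A stronger reading that the text does not support.** A reader might infer from the single table of numbers that allocation is simple and unstratified, and ask for a new blocked list by hospital. The article never says simple, unblocked or unstratified. It condenses a fuller protocol, where blocks and strata would commonly be set out. Recruitment is already in progress (Trial status), so replacing the list midway would leave two allocation schemes to document, on the strength of a defect not shown to exist. The randomisation is therefore not criticised here.

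**Conclusion.** The point holds as a modest matter of efficiency. The stated model omits two candidate prognostic factors in a two-hospital trial with a wide time-since-stroke window. Adding them would cut the standard error by about 1% to 5% and raise power at N = 62 from 0.812 to between 0.82 and 0.85. That range rests on an assumed R² of 2% to 10% and an assumed correlation of 0.5; the documents fix neither. A reader might go further and conclude that the treatment comparison is confounded by hospital or by time since stroke. The documents do not support that: allocation is random, the test remains valid, and sizeable imbalance is possible but not the expected result.

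**What to change.** In the Statistical analysis section, prespecify hospital (fixed effect) and time since stroke onset as covariates alongside the baseline score, for every outcome. Make the change before unblinding, so that the choice cannot look driven by results. The Blinding section keeps the group codes masked until the end of data analysis, which leaves room for this.

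The cost is 2 degrees of freedom, with time since onset entered as a single linear term. Hospital is known from the recruiting site, and onset has to be established to apply the 1-year eligibility limit. The case report form is not shown, so confirm that the onset date itself is recorded and not only that the criterion was met. No change to the randomisation list or the sample size is needed.

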**Fig. 1 Fig1:**
[figure not shown]
Flow diagram of the study design

**Fig. 2 Fig2:**
[figure not shown]
SPIRIT figure showing time points for enrollment, allocation, interventions and assessment. t_-1_ = − 2 week, 0 = baseline, t_1_ = start of treatment week 1, t_2_ = end of treatment week 12, t_3_ = follow-up week 24

### Setting and recruitment

All participants will be recruited at Yueyang Hospital of Integrated Traditional Chinese and Western Medicine and Shanghai Jinhui Rehabilitation Hospital. Both hospitals will post research advertisements to recruit participants. To enhance recruitment quality, the chief investigator will monitor medical records. Recruitment will be carried out by two study researchers, who will carefully record the participants’ past and present medical history.

### Ethical review and general statements

This trial was approved by the Ethics Committee of Yueyang Integrated Hospital of Traditional Chinese and Western Medicine (approval number: 2019-026) and registered in China Clinical Trial Registration Center in October 2019 (registration number: ChiCTR1900026532). All participants will provide written informed consent according to the Helsinki Declaration before participating.

### Eligibility criteria

#### Inclusion criteria

The eligible patients have to meet the following criteria: (1) the clinical diagnosis of stroke according to the Fourth National Academic Conference on Cerebrovascular Diseases Diagnostic Criteria for All Kinds of Cerebrovascular Disease [14] and confirmed by CT or MRI, (2) within 1 year of onset, (3) aged 60–75 years, (4) mild cognition impairment: MoCA< 26 (if the length of schooling is ≤ 12 years, then 1 point will be added to the examination result), (5) balance function: 21 < Berg score < 40, and (6) agreement on participation and signing the informed consent.

#### Exclusion criteria

The exclusion criteria are as follows: (1) patients who are experiencing a severe medical condition, such as heart, liver, kidney, or endocrine diseases; (2) patients with aphasia or hearing impairment; (3) participants of other clinical trials; and (4) patients who are currently using medications to improve cognitive functions.

#### Withdrawal or dropout criteria

Participants demands to withdrawal from the study;Participants are diagnosed with other severe disease;Participants showed adverse reactions to the treatment.

### Randomization and allocation concealment

To reduce the chance of bias and increase the probability of meeting statistical analysis assumptions, the chief investigator will receive a computer-generated random list using the statistical software SPSS 24.0 from a statistician independent of the analysis and research teams. Then, the chief investigator will inform the coaches, therapists and participants about the treatment and follow-up plan. Before the first treatment and after the treatment is completed, the assessors will be notified to evaluate all participants.

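### The random list goes to the chief investigator, who also has a role in recruitment, so foreknowledge of assignments is possible

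*Protocol article*

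**What the plan says.** The relevant statements are in four sections of the protocol article.

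- **Study design:** "SPSS software will generate a table of numbers that will be used to randomly assign all eligible patients", at a 1:1 ratio. The sequence therefore exists as a prepared table.
- **Randomization and allocation concealment:** "the chief investigator will receive a computer-generated random list using the statistical software SPSS 24.0 from a statistician". The list comes "from a statistician independent of the analysis and research teams". The next step is: "Then, the chief investigator will inform the coaches, therapists and participants about the treatment and follow-up plan".
- **Setting and recruitment:** "To enhance recruitment quality, the chief investigator will monitor medical records". The contact with patients belongs to others: "Recruitment will be carried out by two study researchers, who will carefully record the participants’ past and present medical history".
- **Blinding:** coaches and participants cannot be blinded. Assessors and data analysts work with group codes A and B, whose meaning is revealed by an independent research assistant at the end of the analysis.

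**The concern.** Allocation concealment means that nobody who can affect whether, or when, a patient enters the trial knows the next assignment. The section that carries this heading describes one custody step, and that step gives the list to someone with a stated part in recruitment.

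If the list holder can foresee the next arm, a patient with a better or worse outlook can be accepted, deferred or declined accordingly. The arms then differ in prognosis before treatment starts. Adjusting for the baseline score, as planned under Statistical analysis, removes only the part of that difference that the baseline score captures, and a larger sample removes none of it. The comparison at stake is the primary one on the MoCA, in a trial of 72 patients whose Discussion already expects the exercise group to do better.

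**Working it through.** No figure in the plan is at issue, so the check is to set the sections side by side.

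1. **Who makes the list?** A statistician outside the analysis and research teams. Generation is sound.
2. **Who holds it afterwards?** The chief investigator, by the direct statement in "the chief investigator will receive a computer-generated random list using the statistical software SPSS 24.0 from a statistician". This is a stated rule. It is not inferred from something the article leaves out.
3. **Does the holder have a role before allocation?** Yes, to a degree. Setting and recruitment says that "the chief investigator will monitor medical records" for the sake of recruitment quality. That gives access to prognostic information on candidates. It does not expressly give the decision to enrol.
4. **Is there room for judgement in eligibility?** Yes. The Exclusion criteria refer to severe heart, liver, kidney or endocrine disease without stating a threshold, so a review of records could bear on who enters.
5. **Who announces the assignment?** The same chief investigator. Custody of the list, review of records and announcement of treatment thus meet in one person.
6. **Does another safeguard in the text close the gap?** The only candidate is the pair of codes under Blinding. These apply to assessors and analysts and act after allocation. They do not hide the next assignment from someone who holds the list.
7. **Do the recruiting researchers see the list?** The article does not say that they do, nor that it is kept from them.

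Steps 2, 3 and 6 together show that foreknowledge is possible at one point in the trial team. Step 7 shows why the text does not establish that enrolment is in fact steered.

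**Size.** If a fraction *p* of each arm were steered, and the expected MoCA change of those patients differed by *d* points between arms, the arm difference would shift by *p* × *d* without any treatment effect. The document gives neither *p* nor *d*, so the shift cannot be calculated from it.

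**The case against.** The strongest reply has four parts.

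**Recruitment is done by others.** Two researchers recruit, and no section gives the chief investigator the decision to enrol. This stands. A reader might infer that the chief investigator runs enrolment and that allocation is simply unconcealed. The text supports less: a list holder with some influence on recruitment, and no stated barrier.

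**The article is a condensed protocol.** Envelopes, central assignment or sequential release may be described in the full document, and their absence here is no finding. This also stands. For the same reason, it is an inference that the chief investigator receives all 72 assignments at once, because the article speaks only of a list. It does not answer the point itself, however: the article chose to describe its concealment step, and the step described puts the list in the hands of someone who should not have it.

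**The baseline order is not established.** A reader might infer that participants learn their arm before baseline is measured, because the sentence on informing them is followed by "Before the first treatment and after the treatment is completed, the assessors will be notified to evaluate all participants". The documents do not support this. That sentence covers assessments both before and after treatment, so it summarises when assessors are called and is not the next step in a sequence. MoCA and Berg scores are inclusion criteria, and Study design randomises eligible patients, so a MoCA score must exist before allocation. A separate, later baseline MoCA is possible but not stated. The SPIRIT figure, which could settle the order, is not available here.

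**Any number would be assumed.** For example, steering 10% of each arm with a 3-point difference gives 0.10 × 3 = 0.3 MoCA point. Both inputs are invented for illustration, so this is no estimate of the bias.

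**Conclusion.** The concern holds as a defect in stated custody. The section meant to secure concealment gives the random list to a member of the trial team who also has a part in recruitment. Neither independent generation nor the A/B codes prevent foreknowledge by that person. Selection bias is possible but not demonstrated, and its size cannot be derived from the document.

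The conclusion rests on two readings: that reviewing records for recruitment quality gives some influence on who enters, and that no unreported device withholds upcoming assignments from the list holder. It does not rest on any claim that the recruiting researchers know the next assignment, or that baseline scores are taken after participants know their arm. The sample size and the analysis model are unaffected.

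**What to change.** **Remaining participants.** The independent statistician, or another person with no part in recruitment, keeps the list and releases one assignment at a time. Each release follows a record that eligibility is confirmed, consent is signed and baseline assessments are complete. Neither the chief investigator nor the recruiting researchers hold the list. Randomization and allocation concealment should state this order: consent and eligibility, baseline assessment, release of the assignment, then informing of participants and staff.

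**Participants already enrolled.** Trial status says that recruitment began in May 2019 and is in progress, so assignments already made cannot be concealed afterwards. The trial report should state who held the list during that period, who could see it, and when baseline was taken relative to allocation.

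**Cost.** A procedural amendment, one message or sealed envelope per remaining participant, and a paragraph in the report. The independent statistician is already in place, and sample size and analysis stay as they are.
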